## Study Design

### Overall Study Design

The PAIRED trial builds upon more than 10 years of research investigating unique motor, cognitive, and symptomatic benefits of PDAE. The study will perform a two arm, randomized controlled trial comparing efficacy of PDAE vs. WALK for improving OFF-time and visuospatial cognition among individuals with PD who report OFF-time. We will randomize *n* = 82 participants equally to 16 months of PDAE (*n* = 41) or to walking as aerobic exercise WALK (*n* = 41) in blocks of two to reduce variability within treatment conditions. Participants will be stratified by sex and Hoehn & Yahr (H&Y) staging (I, II, or III). The 16-month intervention period will consist of Training (3 months) and Maintenance (13 months) phases. In Training, participants will complete 20 biweekly 90-min sessions. In Maintenance, participants will complete 90-min weekly sessions. To evaluate SNc neurodegeneration over the observation period, we will image patients at study entry and 16-month follow-up using fMRI sequences. We will compare SNc volume and iron accumulation estimates in PDAE vs. WALK to assess whether PDAE is more neuroprotective.

Participants will be assessed at baseline, 3 months (immediately post-Training), and at 16 months (immediately post-Maintenance) for OFF-times, cognition, and neuroprotection, as evaluated in the SNc. At a standardized time of day, participants will be tested on all outcome measures at least 12 h after their last dose of antiparkinsonian medications. Furthermore, participants will keep an OFF-time diary to corroborate MDS-UPDRS-IV assessments. Participants will be ON medications during intervention. In addition to the primary motor and cognitive outcome measures, participants will be tested on secondary behavioral motor and cardiovascular and cognitive outcomes. Participants will undergo NM-MRI and fMRI scans at baseline and 3 and 16 months assessments to investigate mechanisms by which cognitive benefits have been obtained and replicated by PDAE and whether PDAE vs. WALK is neuroprotective, as exhibited by slowed rate of NM loss and iron accumulation and increased functional connectivity with spatial cognitive areas.

The proposed study has three aims. Aim 1 will evaluate whether exercise reduces OFF-time in PD patients who regularly suffer OFF-time. Aim 2 will examine the effects of a combined motor/cognitive intervention on cognition, specifically spatial cognition. In Aim 3, with physiological biomarkers, we aim to show that exercise slows neurodegeneration in humans with PD.

Primary outcome variables will be MDS-UPDRS-IV total score (Aim 1), Corsi Blocks product score (Aim 2), and rate of iron accumulation (Aim 3). Secondary outcome variables include motor, cognitive, and neuroanatomical variables. Motor variables include the distance walked during the 6-min walk test and a VO_2_ max measurement (Aim 2) and gait speed; cognitive variables include measures of executive function, attention, and additional visuospatial function measures (Aim 2). Neuroanatomical biomarker variables include the rate of loss of Snc NM volume (Aim 3).

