### Power and Sample Size for the Primary Outcome

The trial is powered for the primary outcome, MDS UPDRS-IV total score. A differential effect size of *d* = 0.89 in the change of OFF-time for PDAE vs. walking using data collected by Uc et al. (30) was observed (Table 1) (30).

Given the study design's 3- and 16-month timepoints, we will use Holm's procedure (62) to control for multiple testing. The alpha levels will be 0.025 and 0.05 for *p*-values in ascending order for comparing PDAE and WALK in the changes from the baseline at 3 and 16 months. The observed effect size (*d* = 0.89) is from participants that finished their programs in the shorter duration pilot studies; therefore, we expect the intent-to-treat effect size will be reduced. Thus, we power the study for an attenuated effect of the observed effect: *d* = 0.7, which is 64% of the observed effect size in our pilot study or 79% of the estimated effect vs. walking, giving us 81 and 88% power for the comparisons at alpha level of 0.025 and 0.05, respectively. With a sample size of *n* = 41 completers per group, total *n* = 82, we additionally expect to have medium to high (60–80%) power to detect differences between the PDAE and WALK groups on the visuospatial outcome (Aim 2), given that the estimated effect size for Corsi Blocks is 0.76 vs. a cognitively engaging contact control (63). We will assume 25% attrition and will therefore recruit 102 participants with PD. For the exploratory variables, we will only focus on effect estimation instead of inference testing given that we do not know the effect size.

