## Intervention

Fidelity will be monitored by the investigators via weekly reports from interventionists and monthly class visits of both investigators. Dose for intervention will be measured by the time spent in the class, e.g., one class is a dose of 90 min. Volume of the intervention is defined as frequency times duration, and therefore, the volume will be ~180 min/week for the Training phase and 90 min/week for the Maintenance phase. The intensity of exercise will be measured with heart rate monitors.

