### Partnered Dance Aerobic Exercise

PDAE has been shown to improve motor function as measured by motor symptoms, balance, preferred, backward and fast gait, mobility, endurance, and QOL (51–56). It is an adapted form of Argentine tango, aka Adapted tango. People with PD partner an individual without PD, e.g., a trained caregiver, friend, or university student. The instructor and several trained assistants will carefully monitor all participants. Class sizes will consist of 10 or fewer pairs of participants with PD and partners to maximize safety. Participants with PD will dance the follower role only and will dance with new partners (individuals without PD) every 15 min, a widely practiced method considered by the dance teaching community to enhance learning. Participants will engage in partnering exercises on how to interpret motor goals through touch, exercises to develop understanding of temporal relationship of movement to music, novel step introduction, and connecting previously learned and novel step elements. Frequent repetition and musical stereotypes may foster implicit learning or muscle memory (i.e., motor learning or procedural memory that involves consolidating a specific motor task into memory through repetition). Participants will not be required to memorize specific step patterns but will learn new steps in each class.

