### Walking Aerobic Exercise

Participants in WALK will receive equivalent dose, volume, frequency, intensity, and duration of exercise to the PDAE group. They will receive equal contact and monitoring from study staff. WALK participants will report to the same facility and interact with the same interventionist and assistants. They will participate in sessions focused on at least 60 min of walking with breaks *ad libitum* and half hour balance and stretching. We have a designated safe and non-cluttered area for walking. WALK will also take place in groups, with research volunteers and assistants to ensure that PDAE and WALK participants both receive a socially engaging intervention.

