### Disease Severity

A blinded MDS-certified rater will administer the MDS-UPDRS parts I–IV at all evaluations. We will videotape Motor Subscale III. The primary outcome, the MDS-UPDRS-IV score (71), measures MRMF including dyskinesias, OFF-time, functional impact and complexity of fluctuations, and dystonia. We will administer a monthly OFF-state diary (72) for corroboration.

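### Fixed blocks of two within sex-by-stage strata let anyone who tracks allocations in a stratum deduce the second assignment of each pair

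*Protocol article*

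**What the plan says.** The Overall Study Design section fixes equal allocation "in blocks of two to reduce variability within treatment conditions". The next sentence adds the strata: "Participants will be stratified by sex and Hoehn & Yahr (H&Y) staging (I, II, or III". Two sexes by three stages gives six strata.

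The interventions are visible to those who take part and those who run them. In the dance arm, "Participants with PD will dance the follower role only and will dance with new partners". In the walking arm, "WALK participants will report to the same facility and interact with the same interventionist and assistants". The Intervention section has fidelity monitored through "weekly reports from interventionists and monthly class visits of both investigators", so the investigators also see who is in which class.

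Blinding is described for raters, assessors and analysts. For the primary outcome, "A blinded MDS-certified rater will administer the MDS-UPDRS parts I–IV at all evaluations". The Analyses section considers sex and H&Y stage (below III versus III or above) as covariates.

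The number randomised is given in two ways. Overall Study Design says "We will randomize *n* = 82 participants equally to 16 months of PDAE", with 41 per arm. The power section treats 82 as completers and says "We will assume 25% attrition and will therefore recruit 102 participants with PD", and the Abstract also randomly assigns 102. That conflict is a separate matter. Both totals are carried below and the conclusion is the same for each.

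**The concern.** At 1:1, a block of two has only two possible orders, dance then walking or walking then dance. Once the first allocation of a pair is seen, the second is certain. Sex and H&Y stage are known before randomisation (stage is an eligibility criterion), so a recruiter can tell which stratum a candidate will enter. The block size is published.

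Concealing the list does not help, because the deduction uses earlier allocations that are visible in the classes and not the list.

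At stake is selection at entry. Someone who knows the next arm could hasten, delay or discourage a candidate according to enthusiasm, fitness or likely attendance. The Participants section leaves room for discretion: 656 people are to be contacted, about one in five of those approached is expected to join, and they come from several clinics, community sources and a registry. Differences created this way precede the outcome rating, so a blinded rater cannot remove them, and they are not captured by sex and H&Y stage. With 25% attrition assumed, selection on expected attendance could also make dropout differ between arms.

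**Working it through.** The article gives no figure for predictability, so there is none to reproduce. Its power figures (81% and 88% for d = 0.7 with 41 per arm) do reproduce, at 81.0% and 87.9% by a two-sided t-test, and do not depend on this point.

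**Inputs.** From the article: block size 2, ratio 1:1, six strata, N = 82 or 102. Assumed: participants are allocated one at a time, and the observer knows the block size and the earlier allocations in the stratum.

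**Completed blocks.** For a block of size 2m with m per arm:

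- Share of assignments certain from earlier ones = 1/(m + 1).
- Expected correct guesses per block, always guessing the arm that is behind = m + 2^(2m−1)/C(2m, m) − 1/2.

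| Block size | Certain | Correct guesses per block | Share correct |
|---|---|---|---|
| 2 | 1/2 = 50% | 1 + 2/2 − 0.5 = 1.5 | 75% |
| 4 | 1/3 = 33% | 2 + 8/6 − 0.5 = 2.83 | 70.8% |
| 6 | 1/4 = 25% | 3 + 32/20 − 0.5 = 4.1 | 68.3% |

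**Six strata with blocks of two.** A stratum of odd size ends on an unfinished block, so the certain assignments number (N − number of odd strata)/2. If about half of the six strata are odd:

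- N = 82: (82 − 3)/2 = 39.5, or 48.2%. Correct guesses: 39.5 + 0.5 × 42.5 = 60.75, or 74.1%.
- N = 102: (102 − 3)/2 = 49.5, or 48.5%. Correct guesses: 49.5 + 0.5 × 52.5 = 75.75, or 74.3%.

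The article does not give the stratum split. Simulation with 1,500 runs per scenario under two assumed splits (equal sixths; 70/30 by sex with 15/60/25 by stage) gave the same results: 48% and 49% certain, 74% guessed. Simple randomisation would give 50% guessed.

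**Alternatives, six strata, N = 82, by simulation.** Fixed blocks of 4: about 30% certain, 69% guessed. Fixed blocks of 6: about 21% certain, 67% guessed. Random blocks of 4 and 6: about 68% guessed, and no assignment certain from block size alone as long as the sizes are unknown. Someone who learned that the sizes were 4 and 6 would regain some certainty. For example, three allocations to one arm at the start of a block would identify a block of six and fix the next three.

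**Imbalance.** The largest possible imbalance is 1 per stratum with blocks of 2 and 3 with blocks up to 6. Over six strata that is 6 against 18. Strata average 82/6 = 13.7 or 102/6 = 17 participants. Effective sample size is 4·n1·n2/N. At N = 102 the worst split is 60 against 42: 4 × 60 × 42/102 = 98.8, a loss of about 3%. At N = 82 it is 50 against 32: 4 × 50 × 32/82 = 78.0, a loss of about 5%.

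**Illustration of what selection could do (assumed, not evidenced).** Suppose that, in the half of assignments that are certain, candidates' expected outcomes are shifted by s SD in favour of dance and s SD against walking. The bias is 0.5 × 2s = s. For s = 0.1 this is 0.1/0.7 = 14% of the design effect, and with 41 per arm and no true effect the nominal 5% error becomes about 7%. For s = 0.2 it becomes about 15%.

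**The case against.** Several objections have force.

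- **Reach.** A reader might infer that every second assignment in the trial is known in advance. The document does not support that. The deduction works only within a stratum, and only for someone who keeps track of six separate sequences.
- **Who knows.** The article says that the same people deliver both arms and that investigators visit classes. It does not say that these people screen, consent or request allocations. It also does not say whether participants are allocated singly or in batches for group classes. If both members of a pair were enrolled before either was allocated, the risk would vanish. An article may leave such procedures to the full protocol, and the absence of a described concealment method is no finding. The point rests only on the block size that the article does state.
- **Self-report.** A reader might infer that a participant-reported outcome carries selection straight into the treatment difference. Selection acts through prognosis at entry whether or not the outcome is self-reported. Unmasked reporting is a different issue, and block size does not change it.
- **Mitigation.** The blinded certified rater, the analysis of change from baseline and the covariates are real strengths. They do not remove selection on enthusiasm or expected attendance.
- **Benefit and cost.** Best-guess accuracy falls only from about 74% to 68%; the larger gain is the loss of certainty. Short blocks are commonly chosen because strata are small, so imbalance must be judged against strata of about 14-17 on average, some perhaps much smaller, and not against the arm size.
- **Rationale.** The wording about variability is a minor error and changes nothing in conduct or analysis.

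**Conclusion.** The point stands as an avoidable design risk. With blocks of two in six strata, about 48-49% of assignments (50% if all blocks complete) can be deduced by someone who tracks allocations within the stratum, and about 74-75% can be guessed correctly. This rests on sequential single allocation, on knowledge of the published block size, and on seeing earlier allocations, which the unmasked arms and shared staff make possible. That the trial is unmasked for participants and interventionists is inferred from the interventions; the article does not use the term open-label. Nothing in the document shows that enrolling staff hold or use this knowledge, or that bias has occurred. Because the remedy is cheap, it should be adopted. The stated reason for the blocks should be corrected as well.

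**What to change.** Replace the fixed blocks of two with computer-generated permuted blocks of randomly varying size, for example 4 and 6, within the existing sex-by-H&Y strata. Withhold the sizes from recruiting and intervention staff, which also means keeping them out of documents that those staff can read during enrolment. Correct the rationale to say that blocking keeps the arm numbers balanced over time. If enrolment has begun, apply the new blocks to participants not yet randomised.

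The cost is a new randomisation list and somewhat more possible imbalance: up to 3 instead of 1 per stratum and, in the worst case, 18 instead of 6 overall. Even then the loss of effective sample size is about 3% at 102 randomised, or about 5% at 82.

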**Primary study outcomes**				
MDS UPDRS-IV	Motor complications	**2.23 (2.4)**	−0.3 (1.9)	1.09
Corsi product score	Spatial cognition	**6.9 (11.0)**	−3.4 (16.0)	0.76
**B. Outcome**	**Domain**	**PDAE**	**WALK^*^**	**d, PDAE vs. WALK**
OFF-time (30)	Motor complications	**2.23 (2.4)**	0.4 (1.7)	0.89

* *Data from (30); change scores >0 indicate improvement. Bold numbers indicate which group improved most*.

We explain the premise for expected improved spatial cognition and correlating measurable changes in the CNS. In our published study (56), 23 PDAE participants improved significantly on disease severity (*p* = 0.008; $\eta_{\text{p}}^{2}$ = 0.148) and spatial cognition (*p* = 0.021; $\eta_{\text{p}}^{2}$ = 0.121) compared to eight Education participants. PDAE participants also improved in executive function (*p* = 0.012; $\eta_{\text{p}}^{2}$ = 0.133). Gains were maintained 3 months postintervention. Table 1 reveals additional data from our lab comparing a contact control group (Education) vs. 18 randomly assigned participants who completed 30 h of PDAE for 3 months. Analyses of measures from the cognitive spatial domain using Corsi blocks assessment at pre- and post-20 lessons reveal a large effect between change scores of the Education group and the PDAE group (*d* = 0.76; Table 1).

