### Analyses

#### Aim 1

We will analyze the primary study outcome with a mixed effect model (treating subject as random) with between-subjects effect of group (PDAE vs. WALK) and within-subjects timepoints (study entry, 3-month follow-up, 16-month follow-up) plus their interaction term. If the interaction term is significant, we will test differences between PDAE and WALK in the change from baseline to 3 months and from baseline to 16 months using Holm's procedure to control for multiple testing. We will consider covariates sex and H&Y staging (<III, ≥III) in the analyses.

#### Aim 2

The secondary outcome Corsi Blocks Score will be analyzed using a similar mixed effects model.

#### Aim 3

We will use similar analyses. We will use mixed effects model except that it will be a two-group (PDAE vs. WALK) and a two-level variable for time (study entry vs. 16-month follow-up).

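### Three outcomes are listed as primary in one place and one in others, and Corsi Blocks is labelled both primary and secondary; the labels should be aligned on MDS-UPDRS-IV

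*Protocol article*

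**What the plan says.** The protocol article gives two accounts of which outcomes are primary.

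*More than one primary outcome*
- Overall Study Design, outcome list: "Primary outcome variables will be MDS-UPDRS-IV total score (Aim 1), Corsi Blocks product score (Aim 2), and rate of iron accumulation (Aim 3"). The secondary outcomes are listed separately and include neither Corsi Blocks nor iron accumulation.
- Overall Study Design, paragraph on assessments: secondary measures are set against primary measures of both a motor and a cognitive kind.
- Table 1 (Introduction, pilot data): the Corsi product score stands beside MDS-UPDRS-IV under the row heading "Primary study outcomes".

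*One primary outcome*
- Power and Sample Size for the Primary Outcome: "The trial is powered for the primary outcome, MDS UPDRS-IV total score".
- Disease Severity: "The primary outcome, the MDS-UPDRS-IV score (71), measures MRMF including dyskinesias, OFF-time, functional impact and complexity of fluctuations, and dystonia".
- Analyses, Aim 1: the primary study outcome is mentioned in the singular, and under this aim only.
- Analyses, Aim 2: "The secondary outcome Corsi Blocks Score will be analyzed using a similar mixed effects model".

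*Multiplicity*
- Power section: "Given the study design's 3- and 16-month timepoints, we will use Holm's procedure (62) to control for multiple testing". The levels follow: "The alpha levels will be 0.025 and 0.05 for *p*-values in ascending order for comparing PDAE and WALK in the changes from the baseline".
- Analyses, Aim 1, puts an overall test first: "If the interaction term is significant, we will test differences between PDAE and WALK in the change from baseline to 3 months", and likewise to 16 months, with Holm across the two contrasts.
- No testing order, alpha split or success rule across the three outcomes is given. No alpha is stated for Aims 2 and 3.

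**The concern.** For Corsi Blocks, the outcome list and the Aim 2 analysis contradict each other. Whoever reports the trial could cite the document for either status. If MDS-UPDRS-IV is null and Corsi or iron is positive, the outcome list supports calling that a positive primary result. If Corsi is null, the analysis section supports calling it secondary. The Introduction states a superiority hypothesis in all three domains (OFF-time, spatial cognition, neurodegeneration), so each result will be looked at with a claim in mind.

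The power section's restriction to effect estimation covers exploratory variables only. It therefore does not restrain claims on Corsi or iron under either label.

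At stake is whether the 5% level that Holm protects for MDS-UPDRS-IV is also the error rate of the trial's primary claim.

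**Working it through.** **1. The plan's own power figure.** Inputs from the power section: 41 completers per arm, d = 0.7, alpha 0.025 and 0.05. Two-sided testing and equal variances are assumed.

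Noncentrality = d × √(n/2) = 0.7 × √(41/2) = 3.169, with 2 × 41 − 2 = 80 degrees of freedom.

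| Alpha | Normal approximation | Noncentral t | Stated |
|---|---|---|---|
| 0.025 | Φ(3.169 − 2.241) = 82.3% | 81.0% | 81% |
| 0.05 | Φ(3.169 − 1.960) = 88.7% | 87.9% | 88% |

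The figures reproduce. They use the whole 5% on MDS-UPDRS-IV, split only over two time points.

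**2. Power if three primary outcomes shared the 5%.** Bonferroni gives 0.05/3 = 0.0167 per outcome and a first Holm step of 0.0167/2 = 0.0083. With 41 per arm and d = 0.7, noncentral t power for MDS-UPDRS-IV is 76% at 0.0167 and 68% at 0.0083. The stated 81% and 88% therefore fit only a single primary outcome.

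**3. Familywise error with one primary outcome.** Holm over two contrasts at family level 0.05 holds it at no more than 5%.

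**4. Familywise error if all three were primary.** Assumptions, none stated in the protocol: each outcome is tested at 0.05, any one counts as success, and all nulls are true.
- Independent outcomes: 1 − 0.95³ = 14.3%.
- Upper bound whatever the dependence: 3 × 0.05 = 15%.
- Pairwise correlation 0.2, 0.5 and 0.8 (simulated): 14.0%, 12.5% and 9.9%.

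**5. The same with the plan's own interaction test and Holm step applied to Aims 1 and 2.** For each of these outcomes, a false win needs a significant interaction and a significant Holm contrast. Simulation gives 3.8%, 3.6% and 3.2% at assumed correlations between the time points of 0.3, 0.5 and 0.7. With iron at 5% and independent outcomes:
- correlation 0.3: 1 − (1 − 0.038)² × 0.95 = 12.1%
- correlation 0.5: 11.7%
- correlation 0.7: 11.0%

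**The case against.** The strongest reply is that the sections that set the inference agree. The power section, the Disease Severity section and the Aim 1 analysis all name MDS-UPDRS-IV alone, and the outcome list can be read as giving the lead measure for each aim. This largely stands: the intended primary outcome can be identified. It does not remove the contradiction, because the outcome list uses the word primary for Corsi and the Aim 2 analysis uses secondary.

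A second reply is that testing order across outcomes is commonly left to a statistical analysis plan, which is not shown. That also stands, so the absence of such an order is not the point. Which outcome is primary is settled in the protocol, and here it is stated two ways.

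Four stronger readings are tempting, and the document does not support them.
- A reader might infer that the trial has no single success criterion. The power and Aim 1 analysis sections point to one.
- A reader might infer that the trial's error rate is 14%. That needs three primary outcomes, each at 5%, any one sufficing, and independence. The protocol does not state this combination.
- A reader might infer that Holm is confined to MDS-UPDRS-IV, leaving the two Corsi time points unadjusted. Aim 2 is described as using a similar model directly after the Aim 1 procedure, so Holm may well carry over.
- A reader might take the lack of a power figure for iron as a further defect. A condensed article need not give power for every aim, and this one says it is powered for MDS-UPDRS-IV.

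**Conclusion.** The labelling contradiction is real. Corsi Blocks is primary in the outcome list and Table 1 and secondary in the Aim 2 analysis. Iron accumulation is primary in the outcome list, while other sections speak of a single primary outcome. The sample size and the Holm step are consistent only with MDS-UPDRS-IV as sole primary.

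The size depends on the reading. With MDS-UPDRS-IV as sole primary, the familywise error of the primary claim is at most 5%. With three primary outcomes, each at 5% and any one sufficing, it is about 10% to 14% over correlations from 0.8 down to 0, and never above 15%. With the plan's interaction test and Holm step applied to Aims 1 and 2, it is about 11% to 12% for independent outcomes. The multiple-primary figures describe what the outcome list would allow, not a rate the protocol fixes. The contradiction should be removed before any outcome data are seen by group.

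**What to change.** In Overall Study Design (both the outcome list and the paragraph on assessments) and in the Table 1 heading, name MDS-UPDRS-IV total score as the only primary outcome. List Corsi product score and rate of iron accumulation as key secondary outcomes, reported as supportive and without a confirmatory claim. The power section, Disease Severity section and Analyses section then agree as they stand.

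If confirmatory claims on the secondary outcomes are wanted, fix the order as MDS-UPDRS-IV, then Corsi (with Holm over 3 and 16 months), then iron. Move to the next outcome only when both Holm-adjusted time-point contrasts of the preceding one are significant.

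Requiring both matters. Suppose one significant time point were enough, the 3-month effects on MDS-UPDRS-IV and Corsi were real and almost certain to be detected, and both 16-month contrasts and iron were null. Three true nulls would each be tested at 0.05, and under independence the error would again be 1 − 0.95³ = 14.3%.

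The cost is wording only, with sample size and assessments unchanged. Corsi and iron lose stand-alone primary status. In the confirmatory version, the chance of reaching Corsi cannot exceed 88% even if d = 0.7 holds at both time points, because each contrast must at least reach 0.05.
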